### Data collection

Data will be collected at the following points:
▪ T1: At the start of treatment/baseline▪ T2: 9 months from baseline▪ T3: Pre alveolar bone graft▪ T4: 3 months post alveolar bone graft▪ T5: 6 months post alveolar bone graft

Records, i.e., study models, intra-oral and extra-oral photographs and a oblique occlusal radiograph will be taken at each time point. A CBCT will be taken at T5 stage.

In addition, the following data will be collected from patients’ notes:
Number of attendances, including failed and cancelled appointmentsOverall treatment durationFrequency of appliance breakages, if anyAny other emergencies

Patients will be required to fill in the Quality of Life questionnaires (CPQ_8-10_) which will inform us how the appliances will affect them as part of the qualitative assessment. The CPQ_8-10_ is a validated questionnaire and has been used in other orthodontic trials.

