### Study setting

The trial will be coordinated from Sree Balaji Dental College, Bharath Institute of Higher Education and Research, India. The trial will be conducted by cleft teams based in three centres across India. Criteria for the selection of sites are based on the previous experience in research and the volume of patients seen. The cleft team at each centre will include an orthodontist, cleft surgeon, paediatrician and cleft nurse.

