### Outcome measures

The primary outcome will be:
Success of alveolar bone graft assessed from CBCT and oblique occlusal (Kindelan method)

The secondary outcome measures will be:
Quality of the dento-occlusal outcome measured on study models using 10-year-old index scoresQualitative assessment using the validated quality of life questionnairesBreakagesQuality-adjusted cost analysis

The operator will record a patient as non-compliant if:
Subject refuses to wear the applianceBreakage of appliance for more than 3 timesMeasurement indicates a lack of clinical progress after 9 months of appliance wear

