#### Radiographs

The oblique occlusal radiographs will be taken at four time points; start of treatment (T1), prealveolar bone graft surgery (T3), 3 months post surgery (T4), and 6 months post surgery (T5).

The CBCT radiograph will be taken at the final data collection point, 6 months post surgery (T5).

The radiographs will be saved with a unique patient ID and transported to the data coordinating centre using an encrypted USBs. They will be securely stored onto a trial-specific computer within the data coordinating centre.

The SPIRIT checklist for the schedule of enrolment, interventions, and assessments is shown in Fig. 2.

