### Study models

The upper and lower impressions along with a wax bite of occlusion which would be obtained at all time points and will be casted with dental stone at the trial sites. The models will then be transported to the data coordinating centre and stored in a secure site.

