### Photographs

A set of seven extraoral and eight intraoral photographs will be obtained at all time points. The photographs will be saved using a unique study ID on an encrypted USB and transported to the data coordinating centre.

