#### Proposed method to ensure the reliability of measurements

Twenty oblique occlusal radiographs will be evaluated with Kindelan index, a week apart to ensure good reliability of the measurement. The Error will be evaluated with the paired *t* test, Bland and Altmann and intra-class correlation coefficient to test both systemic and random errors.

The trial will be conducted in line with Declaration of Helsinki (1964) and reported using the Consolidated Standard of Reporting Trials (CONSORT).

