### Data analysis

Data will be analysed by an independent statistician. A detailed analysis will be planned before the final analysis of the trial. The main features of the statistical plan are mentioned here.

Data analysis will be carried out at the end of the study.

The primary outcome, Kindelan bone-fill index, is an ordinal measure and will be compared between groups using the Mann-Whitney test. Additionally, the outcome will be categorised as successful (grade 1) or unsuccessful (grades 2–4). The chi-square test will be used to compare the categorised outcome between groups.

Independent sample *t* test and 95% confidence intervals will be used for all continuous outcomes, for comparison between the groups. The dichotomous outcomes will be compared using chi-square test and the effect estimates will be reported using relative risk and 95% confidence interval. The qualitative outcomes will be compared using chi-square test.

A multivariable linear regression analysis will be carried out to assess the effect of pre-treatment complexity, gender and orthodontic treatment on the overall quality of alveolar bone graft success. The primary analysis will be on an intention-to-treat principle; the results of all subjects will be accounted for, regardless of the outcome of the treatment.

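### The article gives two conflicting schedules for the oblique occlusal film: one includes a film at T2 (9 months) and the other leaves it out, and no stated use needs it

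*Protocol article*

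**What the plan says.** The Data collection section of the protocol article defines five time points: T1 at baseline, T2 nine months later, T3 before the graft, and T4 and T5 at three and six months after it. It then treats study models, photographs and the oblique film alike: "a oblique occlusal radiograph will be taken at each time point". A CBCT is added at T5.

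The Radiographs section, under Data collection and management, differs: "The oblique occlusal radiographs will be taken at four time points". It lists them as T1, T3, T4 and T5. T2 is absent.

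The two sections that follow keep the full schedule for the other records. Study models: "The upper and lower impressions along with a wax bite of occlusion which would be obtained at all time points". Photographs: "A set of seven extraoral and eight intraoral photographs will be obtained at all time points".

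Both radiograph statements are current text, and nothing else in the visible article reconciles them. The Radiographs section points to Fig. 2 for the schedule, but the figure is not reproduced in the text at hand.

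**The concern.** Both sentences are complete instructions, and a site cannot follow both. The difference is an X-ray in a child, so it should be settled by a stated purpose and not by which paragraph a site happens to read.

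The trial is multicentre ("The trial will be conducted by cleft teams based in three centres across India"), so centres could read the schedule differently and expose children differently. Whichever sentence a centre follows, it departs from the other, and the Protocol compliance section treats recurring deviations as unacceptable. Participants are 8 to 13 years old and already have four oblique films and a CBCT under the shorter schedule. The Discussion gives reducing the burden of care as the trial's goal.

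**Working it through.** **Step 1: count the films under each section.**
- Radiographs: {T1, T3, T4, T5} = 4 films per child. This reproduces the section's own figure of four.
- Data collection: {T1, T2, T3, T4, T5} = 5 films per child.
- The only member of the second set missing from the first is T2. Nothing is missing the other way.

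**Step 2: look for a stated use of a T2 film.**
- Primary outcome (Outcome measures): graft success by CBCT and oblique film. This needs a film after the graft. T4 and T5 are scheduled for that in both versions, and the CBCT is at T5.
- Dento-occlusal outcome (Outcome measures): scored on study models.
- Reliability exercise: "Twenty oblique occlusal radiographs will be evaluated with Kindelan index". It needs 20 films and does not name T2. T4 and T5 alone give 2 × 72 = 144 with full follow-up.
- Regression (Data analysis): this is to "assess the effect of pre-treatment complexity, gender and orthodontic treatment". Complexity before treatment is by name a baseline matter, which T1 covers.
- Non-compliance criterion (Outcome measures): lack of clinical progress after nine months with an appliance. Its timing matches T2, but it names no radiograph and cannot apply to controls, who have no appliance.

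No stated use is found.

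**Step 3: upper bound on the extra films.** Planned recruitment is 72 (Sample size estimation), allocated 1:1.
- Five-point schedule: 5 × 72 = 360.
- Four-point schedule: 4 × 72 = 288.
- Difference: 360 − 288 = 72, or 72/288 = 25% more. At most 72/2 = 36 of these are in controls.
- If ten children are lost, leaving the 62 that the sample size needs, the ceiling depends on when they leave. It is 62 if all ten leave before T2 (310 − 248 = 62) and 72 if all leave after it, because those children have already had the film.

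**Step 4: why this is a ceiling.** T2 is counted from baseline, while T3 to T5 are tied to surgery. The Rationale gives 6 to 15 months for pre-graft orthodontics. Assume that surgery follows at once:
- Orthodontics ending at 9 months: T3 is at 9 months and coincides with T2.
- Orthodontics ending at 6 months: T4 is at 6 + 3 = 9 months and coincides with T2.

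For controls the article gives no date of surgery:
- Surgery at 3 months: T5 is at 3 + 6 = 9 months and coincides with T2.
- Surgery at baseline: T5 is at 6 months, and T2 falls three months after it.

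Where visits coincide, one film can serve both and nothing is added. The number of extra films therefore lies between 0 and 72. Its position in that range depends on how many centres follow the Data collection sentence and on how visits fall, and the article shows neither.

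**The case against.** The strongest reply is that a dedicated section with a named list normally governs over a one-sentence summary, so most sites would take four films and the conflict is only wording. Sites would also work from the full protocol, its schedule and the case report form, and Fig. 2 may settle the matter. This stands as a reason to expect fewer than 72 extra films. It does not remove the conflict: whichever version Fig. 2 matches, one of the two sentences is wrong.

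A second reply is that the T2 film may be intended, with the Radiographs section having dropped it by mistake. A reader might infer from the neighbouring sections that the Data collection sentence is certainly the faulty one. The documents do not go that far. The explicit four-point list, set against the full schedules for models and photographs, makes that reading the more likely one, but it remains an inference. The method of the nine-month progress check is also unspecified, so a radiographic use cannot be excluded. What can be said is that none is stated.

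A third reply is that the count of one extra film per child is too high because T2 may coincide with another visit. This stands in full, and the count is given only as an upper bound.

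**Conclusion.** The conflict is real and confined to T2. A site following the Data collection section could give a child up to one extra oblique film for which the article states no use. The ceiling is 72 films across 72 children, 36 of them in controls. That ceiling assumes that every centre follows that sentence, that every child reaches T2, and that T2 never coincides with another visit.

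A reader might infer that 72 children will each receive an unnecessary exposure, or that the trial's result is at risk. Neither is supported. The true count could be as low as zero. The T4 and T5 oblique films and the T5 CBCT are in both versions, so sample size and the primary analysis are unaffected. The article gives no dose, so the harm can be expressed only as a number of films. The point merits correction because it decides whether a child is X-rayed, not because it threatens the inference.

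**What to change.** Amend the sentence in the Data collection section so that study models and photographs are taken at every time point but the oblique occlusal film only at T1, T3, T4 and T5. Check that the Fig. 2 schedule and the case report form say the same.

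If the sponsor did intend a film at T2, it should state the purpose, limit the film to the children in whom that purpose applies (for an appliance-progress check, the orthodontic arm only), and correct the Radiographs section instead.

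The cost is one sentence and a check of the schedule and form. No visit is added and the analysis does not change. With the first option, up to 72 films are avoided.

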### Data collection and management

All trial data will be recorded on case report forms (CRF). The forms from the trial centre will be securely transported to the data coordinating centre. They will be entered into a trial specific database by the Trial Manager at the data coordinating centre.

#### Radiographs

The oblique occlusal radiographs will be taken at four time points; start of treatment (T1), prealveolar bone graft surgery (T3), 3 months post surgery (T4), and 6 months post surgery (T5).

The CBCT radiograph will be taken at the final data collection point, 6 months post surgery (T5).

The radiographs will be saved with a unique patient ID and transported to the data coordinating centre using an encrypted USBs. They will be securely stored onto a trial-specific computer within the data coordinating centre.

The SPIRIT checklist for the schedule of enrolment, interventions, and assessments is shown in Fig. 2.

**Fig. 2 Fig2:**
[figure not shown]
SPIRIT checklist for the schedule of enrolment, interventions and assessments

### Study models

The upper and lower impressions along with a wax bite of occlusion which would be obtained at all time points and will be casted with dental stone at the trial sites. The models will then be transported to the data coordinating centre and stored in a secure site.

### Photographs

A set of seven extraoral and eight intraoral photographs will be obtained at all time points. The photographs will be saved using a unique study ID on an encrypted USB and transported to the data coordinating centre.

### Data analysis

#### Sample size estimation

The sample size was based on showing a difference between groups for the primary outcome, success as defined by a Grade 1 on the Kindelan bone-fill index. Based on previous research (Paterson et al.), it is estimated that 60% of the treated will have a successful outcome. It is estimated that only 25% of the untreated group will have a successful outcome. With a 5% significance level and 80% power, it is calculated that 31 subjects per group, 62 in total are required for the study. To allow for a 10% non-compliance rate, 72 subjects will be recruited into the study.

#### Proposed method to ensure the reliability of measurements

Twenty oblique occlusal radiographs will be evaluated with Kindelan index, a week apart to ensure good reliability of the measurement. The Error will be evaluated with the paired *t* test, Bland and Altmann and intra-class correlation coefficient to test both systemic and random errors.

The trial will be conducted in line with Declaration of Helsinki (1964) and reported using the Consolidated Standard of Reporting Trials (CONSORT).

### Data analysis

Data will be analysed by an independent statistician. A detailed analysis will be planned before the final analysis of the trial. The main features of the statistical plan are mentioned here.

Data analysis will be carried out at the end of the study.

The primary outcome, Kindelan bone-fill index, is an ordinal measure and will be compared between groups using the Mann-Whitney test. Additionally, the outcome will be categorised as successful (grade 1) or unsuccessful (grades 2–4). The chi-square test will be used to compare the categorised outcome between groups.

Independent sample *t* test and 95% confidence intervals will be used for all continuous outcomes, for comparison between the groups. The dichotomous outcomes will be compared using chi-square test and the effect estimates will be reported using relative risk and 95% confidence interval. The qualitative outcomes will be compared using chi-square test.

A multivariable linear regression analysis will be carried out to assess the effect of pre-treatment complexity, gender and orthodontic treatment on the overall quality of alveolar bone graft success. The primary analysis will be on an intention-to-treat principle; the results of all subjects will be accounted for, regardless of the outcome of the treatment.

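### The protocol defines and sizes the primary outcome as grade 1 success but then names an ordinal Mann-Whitney comparison first, so the stated 80% power belongs only to the chi-square test listed as additional

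*Protocol article*

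**What the plan says.** Under Sample size estimation, the protocol article identifies the primary outcome as "success as defined by a Grade 1 on the Kindelan bone-fill index". The planning rates are binary: "it is estimated that 60% of the treated will have a successful outcome", and "It is estimated that only 25% of the untreated group will have a successful outcome". "With a 5% significance level and 80% power", the result is "31 subjects per group, 62 in total are required for the study". The recruitment target follows: "To allow for a 10% non-compliance rate, 72 subjects will be recruited into the study".

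Under Data analysis, the primary outcome is the Kindelan bone-fill index itself, which "is an ordinal measure and will be compared between groups using the Mann-Whitney test". The binary version comes second: "Additionally, the outcome will be categorised as successful (grade 1", with grades 2 to 4 as unsuccessful, compared by chi-square. No sentence says which of the two comparisons decides the trial. The same section plans a relative risk with 95% confidence interval for dichotomous outcomes, and an intention-to-treat primary analysis.

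**The concern.** The two sections give different primary outcomes: a binary success in one, a four-grade ordinal index in the other. The calculation supports the binary one, while the test named first addresses the ordinal one. A reader who takes the Data analysis section at its word would attach the 80% power to a test for which it was never calculated.

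Two things are at stake. First, the chance of detecting the planned effect depends on which test is the answer. This matters because the Discussion looks towards sparing children the orthodontic phase if the outcome does not suffer, so a non-significant headline result could be read as support for omitting it. Second, with no ranking, the conclusion can depend on which test is put forward when the two disagree.

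**Working it through.** **Inputs from the protocol.** Grade 1 rates of 0.60 (treated) and 0.25 (untreated), 5% significance, 80% power, 31 per group (all Sample size estimation); 1:1 allocation (Randomisation). Sidedness is not stated; two-sided is assumed. If all 72 recruits are analysed, there are 72/2 = 36 per arm.

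**Step 1: reproduce the stated sample size.** Two-proportion formula, pooled variance under the null, no continuity correction:

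n = [z(0.975)·√(2p̄(1−p̄)) + z(0.80)·√(p₁(1−p₁)+p₂(1−p₂))]² / (p₁−p₂)²

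with p̄ = (0.60+0.25)/2 = 0.425:

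- √(2×0.425×0.575) = 0.699, and ×1.960 = 1.370
- √(0.24+0.1875) = 0.654, and ×0.8416 = 0.550
- (1.370+0.550)² / 0.35² = 3.688/0.1225 = 30.1, so 31 per group

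This matches the protocol. Power at 31 per arm is 81% by formula and 82% by simulation. The 80% is therefore that of the uncorrected chi-square test of grade 1 success.

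**Step 2: what the Mann-Whitney test needs.** It responds to the probability that a random treated child has a better grade than a random control, counting ties as half. That needs the whole four-grade distribution in each arm. The protocol fixes only grade 1, so every split over grades 2/3/4 below is an assumption. For example:

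- Equal failure splits (60/13.3/13.3/13.3 v 25/25/25/25): 0.6×0.875 + 0.133×0.625 + 0.133×0.375 + 0.133×0.125 = 0.675
- Only grade 2 moves to grade 1 (60/15/15/10 v 25/50/15/10): 0.6×0.875 + 0.15×0.50 + 0.15×0.175 + 0.10×0.05 = 0.631
- Even shift (60/20/12/8 v 25/25/25/25): 0.6×0.875 + 0.20×0.625 + 0.12×0.375 + 0.08×0.125 = 0.705

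The grade 1 rates are the same in all three, but the effect that the ordinal test sees is not.

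**Step 3: simulated power.** 200,000 trials per scenario, tie-corrected normal approximation, two-sided 5%.

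| Assumed grades 1/2/3/4, treated v control | Mann-Whitney, 31 per arm | Mann-Whitney, 36 per arm | Verdicts differ, 31 per arm |
|---|---|---|---|
| Equal failure splits, 60/13.3/13.3/13.3 v 25/25/25/25 | 72% | 79% | 14% |
| Only grade 2 moves to 1, 60/15/15/10 v 25/50/15/10 | 48% | 54% | 34% |
| As above with more grade 4 when treated, 60/10/10/20 v 25/50/15/10 | 33% | 37% | 50% |
| Even shift, 60/20/12/8 v 25/25/25/25 | 86% | 91% | 9% |

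The chi-square power is about 82% at 31 per arm and 86% at 36 per arm in every row. Other equal splits give 72% to 74% at 31 per arm. An exact proportional-odds shift (odds ratio (0.6/0.4)/(0.25/0.75) = 4.5) gives about 88%. Extreme splits run from about 12% to over 99%.

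**Step 4: the either-test error rate.** With identical grades of 40/25/20/15 in both arms and 36 per arm, at least one test is significant in about 7% of trials.

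**The case against.** The strongest reply is that an ordinal test suits an ordinal index, uses all four grades and can be the more powerful choice: with an even or proportional shift it beats the chi-square test. That stands. A reader might infer from the 48% or 33% rows that the first-named test is badly underpowered. The documents do not support that reading. Those rows rest on assumed splits in which the remaining treated failures are graded worse, on average, than the control failures. With equal splits the shortfall is modest, and it nearly vanishes if all 36 per arm are analysed. Equally, low power does not require harm: in the 48% row grades 3 and 4 are identical in both arms, and the treated failures look worse only because the mildest became successes.

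Two further inferences also fail. One is that the success scale would be left without an effect estimate; the Data analysis section already plans a relative risk with 95% confidence interval for dichotomous outcomes. The other is that the type I error is inflated; that needs a rule of claiming on either test, which the protocol does not state, and even then the rate is only about 7%.

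Finally, the protocol says that a detailed analysis will be planned later, so the ranking might be settled there. This does not remove the point, which is not an omission: two sections of the same article define the primary outcome differently.

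**Conclusion.** The point holds as a contradiction about the primary outcome and its test. The 31 per group and the 80% power belong to the chi-square comparison of grade 1 success, which the Data analysis section lists second. The power of the Mann-Whitney test at the same grade 1 rates has no basis in the document and may be lower or higher than 80%. At 31 per arm, plausible assumed splits give about 48% to 86%, with about 72% for equal failure splits (79% at 36 per arm). The two tests reach different verdicts in about 9% to 50% of trials across the tabulated scenarios. The sample size reproduction is firm, given a two-sided test; all the Mann-Whitney figures depend on the assumed distribution over grades 2 to 4.

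**What to change.** In the Data analysis section, name grade 1 versus grades 2 to 4, tested by the chi-square test that the trial was sized for, as the single primary analysis. Report it with the relative risk and 95% confidence interval already planned, and add the risk difference with its interval. Label the Mann-Whitney comparison of the full index as supportive, carrying no separate claim. This keeps 31 per group and needs only a wording change before database lock. The price is that a favourable ordinal result could not rescue a negative primary result.

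If the ordinal comparison is to stay primary, the Sample size estimation section must state the assumed four-grade distribution in each arm and restate the power, or the sample size, for the Mann-Whitney test. The chi-square comparison then becomes the supportive one. That route is also sound, but it needs planning data on grades 2 to 4 that the article does not give, and it may change the required number.

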### Design

Prealveolar bone graft Orthodontics (PABO) study is a 1:1 parallel group multicentre trial. Children aged between 8 and 13 will be randomised to either pregraft orthodontics group or no orthodontic treatment group. The study design is illustrated in Fig. 1.

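### Quality of life is labelled qualitative, which points a scored questionnaire to a chi-square test, and the only named form carries the age band 8-10 although entry runs to 13

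*Protocol article*

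**What the plan says.** The Outcome measures section of the protocol article lists quality of life among the secondary outcomes and describes it as a qualitative assessment made with validated questionnaires. No other listed outcome carries that label. The Data collection section names one instrument: "Patients will be required to fill in the Quality of Life questionnaires (CPQ_8-10_) which will inform us how the appliances will affect them", and again classes it "as part of the qualitative assessment".

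The later Data analysis section gives three rules for comparing the arms on outcomes other than the Kindelan index:

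- "Independent sample *t* test and 95% confidence intervals will be used for all continuous outcomes, for comparison between the groups".
- Dichotomous outcomes get a chi-square test with a relative risk and 95% confidence interval.
- "The qualitative outcomes will be compared using chi-square test".

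The only model with covariates in that section is a linear regression "to assess the effect of pre-treatment complexity, gender and orthodontic treatment on the overall quality of alveolar bone graft success", so it does not concern quality of life. The section says that a detailed analysis will be planned later, but presents these rules as the main features of the statistical plan.

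On age, the Design section says "Children aged between 8 and 13 will be randomised", and the eligibility criteria give the same limits. No questionnaire version other than CPQ 8-10 is named.

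**The concern.** Two separate problems meet in one outcome.

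**The test.** A questionnaire that yields a score can enter a chi-square test only after it is cut into categories. The article gives no categories or cut-points. Cutting a score discards information, and cut-points left open can be chosen after the data are seen. The rule for continuous outcomes could also claim the CPQ, so one outcome falls under two rules depending on which label is used.

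**The instrument.** The form's name carries the band 8-10, but eligible children are up to 13. If the form does not suit the older children, nothing done at analysis can repair scores already collected.

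Reducing the burden of care is the declared purpose of the trial, and this questionnaire is the listed outcome that records the child's own view. It is nevertheless one of several secondary outcomes. Attendances, treatment duration, breakages and cost also bear on burden.

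**Working it through.** **1. The plan's own figure.** The article gives no effect size or SD for quality of life. Its one sample-size figure is for graft success: 60% against 25%, 5% significance, 80% power, 31 per group. With a two-sided test, pooled variance and no continuity correction:

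n = [1.96·√(2·0.425·0.575) + 0.8416·√(0.60·0.40 + 0.25·0.75)]² / 0.35² = (1.370 + 0.550)² / 0.1225 ≈ 30.1, rounded up to 31 per group.

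The figure reproduces. It supplies the arm size used below and is not itself in question.

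**2. Which rule reaches the CPQ.** Quality of life is the only listed outcome called qualitative. Dichotomous outcomes have their own chi-square sentence, so the sentence on qualitative outcomes must be meant for something else. The CPQ is the most natural candidate. The t-test sentence covers every continuous outcome, and a questionnaire score can be read as one. The text supports both readings and prefers the first by label.

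**3. What cutting the score would cost (illustration).** Assume a normal score, a true difference of d SD, a two-sided 5% test, n per arm, and a split at the pooled median.

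- Score analysed as such: power = Φ(d·√(n/2) − 1.96).
- Median split: the proportions above the cut are p = Φ(d/2) and 1 − p. Power = Φ{[(2p − 1)·√n − 1.96·√0.5] / √(2p(1 − p))}.

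For d = 0.72 and n = 31:

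- Score: 0.72·√15.5 − 1.96 = 2.835 − 1.96 = 0.875, giving 81%.
- Split: p = Φ(0.36) = 0.6406, and the difference in proportions is 0.2812. Then (0.2812·5.568 − 1.386)/0.679 = 0.265, giving 60%.

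| Assumed d | Score, n = 31 | Median split, n = 31 | Score, n = 36 | Median split, n = 36 |
|---|---|---|---|---|
| 0.5 | 50% | 34% | 56% | 39% |
| 0.72 | 81% | 60% | 86% | 67% |
| 0.8 | 88% | 70% | 92% | 76% |

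The columns for 36 per arm correspond to all 72 recruited children being analysed. At 31 per arm the loss is about 16 to 21 percentage points over this range.

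**4. Age against the form's name.** Entry is at 8 to 13 years, and the name gives 8-10, so children aged 11, 12 or 13 at entry are outside the band from the first visit. If ages were uniform, the share aged 11 or over would be 2/5 = 40% (entry from 8.0 to 13.0 years) or 3/6 = 50% (entry up to the 14th birthday). Uniformity is an assumption, as the article gives no age distribution.

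Follow-up adds age. In the orthodontic arm, braces take up to 15 months and the last visit is 6 months after the graft. A child entering on the 13th birthday could therefore be about 13 + 15/12 + 6/12 = 14.75 years at T5. The 15 months do not apply to the control arm. A child entering near the end of age 10 can leave the band during follow-up.

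**The case against.** The strongest reply is that the chi-square sentence never names the CPQ. Qualitative often just means categorical in statistical usage. The Trial monitoring section also speaks of a qualitative component for the views of parents and patients, and the t-test rule would cover a CPQ score. This stands to the extent that a reader might infer that the plan has definitely committed the CPQ to chi-square, and the article does not go that far. But the reply shows only that the text allows two tests for one outcome, which is itself a reason to correct it.

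A reader might also infer that the absence of baseline adjustment is an error. The documents do not support that. An unadjusted comparison in a randomised trial is valid, and covariates for secondary outcomes are commonly left to the analysis plan. The records that the Data collection section places at every visit are study models, photographs and radiographs. The text does not say at which visits the CPQ is completed, and the schedule figure is not shown. Adjustment for a T1 score would be a gain if such a score exists. That gain is separate from the loss caused by cutting the score.

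On age, three limits stand: the band is read from the instrument's name alone, the 40-50% share is not a figure of the trial, and long brace treatment affects one arm only. The mismatch between the form's name and the entry ages remains on the face of the article.

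**Conclusion.** The point holds in two parts.

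First, the article's labels direct a scored questionnaire most naturally to chi-square while leaving a t test open, and the wording should be corrected so that the score is analysed. The size of the loss, about 81% against 60% power at 0.72 SD with 31 per arm, rests on an assumed effect, a normal score and a median split. The article supplies none of these.

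Second, children aged 11-13 at entry are outside the band in the form's name, so the claim of a validated questionnaire does not evidently extend to them. How many children this affects is unknown. It does not follow that their scores are invalid, because the article does not state the validated range.

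Both parts concern a secondary outcome. The primary outcome, its analysis and the sample size are untouched.

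**What to change.** 1. **Analysis wording.** State in the Data analysis section that the CPQ is analysed as a score, by the between-arm mean difference with 95% confidence interval from a linear model. Adjust for gender, which is the stratification factor, and for the T1 score if the CPQ is completed at T1. State at which visits the form is given, and name the outcomes, if any, that the chi-square sentence on qualitative outcomes is meant to cover. This costs a few lines of text.

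2. **Instrument.** Use a questionnaire version suited to the child's age for older children. The article names none, so the sponsor must confirm which one applies. Assign the version by age at entry, standardise scores within version before pooling, and include version as a covariate. The cost is a second form and a result in SD units instead of questionnaire points. Children who cross the band during follow-up would remain on their entry version, and this should be acknowledged as a limitation.

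3. **If a second version cannot be used.** Keep the single form, report children aged 8-10 at entry separately, and limit the claim of validation to them. This costs precision in that subgroup but needs no new form.
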